### Efficacy measures

The primary efficacy measure will be HbA1c at 12 months.

Secondary efficacy measures will include HbA1c at 3, 6 and 9 months; Total cholesterol at 3, 6, 9 and 12 months; Weight; BMI; Waist circumference; Hypoglycaemia (symptomatic/confirmed/nocturnal/severe - requiring third party involvement); Hyperglycaemic events; Time to insulin treatment; medication use; Health-related utility (EQ-5D), disease-specific quality of life (ADDQoL), depression score (PHQ-9) and use of health care resources; Percentage of persons achieving target of HbA1c ≤ 53 mmol/mol (≤7%); Time to reach HbA1c target; Acceptability of SMBG (measured by SMBG8/SMBG14 questionnaire).

### Safety evaluations and data monitoring

The Data Monitoring Committee (DMC) will monitor the overall conduct of the trial, safeguarding the interests of the trial participants and assessing the safety and efficacy of the intervention. The HbA1c results reported weekly by the accredited central laboratory will be monitored by a sub-committee of the DMC to ensure any participant in the control group whose HbA1c level deteriorates by more than 15% over a 6 month period or exceeds 119 mmol/mol (13%) is flagged to their GP via their local study site. The actual result will not be reported to the local study team or any member of the participant’s health care team until the participant has completed the study.

### Sample analysis

All samples will be analysed in a central accredited diabetes laboratory, the Diabetes Research Unit Cymru laboratory based at Swansea University. HbA1c will be measured using both the Diabetes Control and Complications Trial (DCCT) aligned method and the International Federation of Clinical Chemistry and Laboratory Medicine (IFCC) standardised values [31].

### Statistical analysis plan

The study will be analysed on a comparative basis. All significance tests will be two tailed and carried out at the 5% level. All available data from withdrawn subjects will be included in the analysis up to the time of withdrawal where possible. All statistical hypothesis tests will be performed at a 5% significance level.

The primary objective of the trial will involve the analysis of HbA1c values at 12 months. These values will be checked for Normality, applying suitable transformations as necessary. The values will then be analysed using a general linear model with baseline values and a nested set of group identifiers included as explanatory covariates and factors. The efficacy of the intervention will be assessed by appropriate hypothesis tests on parameters for group identifiers, with suitable allowance for multiple comparisons.

Variables associated with secondary efficacy measures will be summarised and analysed using the approach outlined above for the primary measure, with linear models used for continuous outcomes and binary logistic regression models used for binary outcomes.

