#### Visits 3–6 (3, 6, 9 and 12 months after visit 2)

During these visits the study nurse will carry out a review of the participant similar to Visit 2. Procedures will include collection of clinical data, details of current treatment, blood sample for measurement of HbA1c and total cholesterol, patient reported outcomes (EQ-5D & PHQ-9) and review of participant diaries. Participants will be asked to complete the ADDQoL questionnaire at visits 4 and 6 (6 and 12 month follow up visits) and the ADKnowl questionnaire at visit 6 (12 month follow up visit). For those in the SMBG groups, the study nurse will review the blood glucose readings and discuss and agree a care plan for the next 3 months at each visit. Participant diaries will be collected at the final visit.

The results from the study venous blood samples taken will not be fed back to the participant, the study nurse or any member of the participant’s health care team in order to keep the primary outcome measure (HbA1c) blinded across all treatment groups.

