In addition to the education and support given to the Group 2 participants (SMBG Alone), Group 3 participants (SMBG with Telecare) will be in regular contact with their study nurse. Between the 3 monthly study visits the participants will verbally report or upload their SMBG results to the database (if using the software) for the nurse to review on a monthly basis. Each month, the study nurse will contact the participant by phone and review the blood glucose readings, discussing any trends of glycaemic abnormalities. A care plan is then devised and agreed with the participant for the coming month.

Initiation and adjustment of therapy will be based on the consensus statement from the ADA/EASD [30]. The aim of treatment will be to obtain HbA1c 53 mmol/mol (<7%) and fasting glucose <6.0 mmol/L and 2 h post-prandial glucose <10 mmol/L. Initiation of insulin will be considered if HbA1c is 69 mmol/mol (>8.5%), however, once a participant starts on insulin they will no longer participate in the study.

Blood glucose measurements will be taken on two days of every week during the study by all the participants in both SMBG groups (groups 2 & 3) which will include a weekday and a day at the weekend. Blood glucose will be measured fasting and 2 h after breakfast, and pre and 2 h post the evening meal. In addition, in the week prior to clinic attendance (study visit) participants will perform a 7 point blood glucose profile (pre and 2 h following major meals, and bedtime) on three days. At the clinic visits the meters will be downloaded and calibrated.

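### The stated primary model uses only 12-month HbA1c, so participants who leave early drop out of the primary result although their interim HbA1c is measured

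*Protocol article*

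**What the plan says.** The Statistical analysis plan section makes a general statement about withdrawals: "All available data from withdrawn subjects will be included in the analysis up to the time of withdrawal where possible". It then sets out the primary analysis. "The primary objective of the trial will involve the analysis of HbA1c values at 12 months", and after a check for Normality "The values will then be analysed using a general linear model with baseline values and a nested set of group identifiers" as explanatory terms. No repeated-measures term and no imputation step is named.

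HbA1c is also measured at the interim visits in every arm. Under Visits 3–6: "Procedures will include collection of clinical data, details of current treatment, blood sample for measurement of HbA1c". Under Efficacy measures these values have secondary status: "Secondary efficacy measures will include HbA1c at 3, 6 and 9 months". Secondary measures are to be "analysed using the approach outlined above for the primary measure", which means a separate model for each time point.

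Under The intervention, insulin may be considered above an HbA1c threshold of 8.5%, and "once a participant starts on insulin they will no longer participate in the study". The Sample size section counts insulin converters within the drop-out allowance.

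**The concern.** A linear model of the 12-month value needs a 12-month value. A participant who leaves after the month 6 visit has three HbA1c measurements (baseline, 3 and 6 months) but no outcome in this model, and so does not enter the primary comparison. The statement about withdrawn participants is then met only by the secondary analyses.

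Two things are at stake. The first is information: measured HbA1c that predicts the missing 12-month value is not used. The second is bias. The completers' model is valid if, given baseline and arm, leaving is unrelated to the 12-month value. Exit on starting insulin makes that doubtful, because people start insulin when their glycaemia is poor during follow-up, not only at baseline. If poorly controlled participants leave one arm more readily than another, the remaining participants are no longer comparable.

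**Working it through.** **1. Reproduce the sample size and its implied drop-out.** Inputs from the protocol's Sample size and Statistical analysis plan sections: two-sided 5% level, power 0.8, 378 SMBG to 189 control (2:1), effect size 0.25 and later 0.333.

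Control n = (1 + 1/2) × (1.96 + 0.8416)² / d², with (1.96 + 0.8416)² = 7.849.

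- d = 0.25: 1.5 × 7.849 / 0.0625 = 188.4, so 189 control + 378 SMBG = 567. Then 567 / (1 − 1/3) = 850.5; stated 850.
- d = 1/3: 1.5 × 7.849 × 9 = 105.96, so 106 + 212 = 318. Then 318 / 0.80 = 397.5, rounded up to 398, and 318 / 0.75 = 424. Both match the stated range.

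The protocol gives no figure for the revised drop-out. Its range of 398 to 424 corresponds to 20% and 25%.

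**2. Participants outside the primary model.** 0.20 × 450 = 90 and 0.25 × 450 = 112.5, so about 90–112.

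**3. Where an early leaver's data go.** For someone who leaves after month 6, the 3-month and 6-month secondary models include the data. The 9-month and 12-month models do not.

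**4. Size of the bias.** This needs assumptions that are not in the protocol. The main simulation used 150 control and 300 SMBG participants, SD 1.2% and mean 8.7%. The true 12-month effect was −0.40 (0.333 × 1.2), meaning the effect had everyone stayed. Visit correlation was 0.6 or 0.8 with AR(1) decay. Leaving was possible after months 3, 6 and 9, with HbA1c-related exit following a logistic function of the last observed HbA1c. There were 300 runs per case, so the Monte Carlo error of each mean is about 0.13 / √300 = 0.008. Pairs are for correlation 0.6 / 0.8.

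| Exit pattern | Drop-out, control | Drop-out, SMBG | 12-month model | All-visits likelihood model | Bias of 12-month model |
|---|---|---|---|---|---|
| Unrelated to HbA1c | 25% / 25% | 24% / 24% | −0.391 / −0.396 | −0.393 / −0.394 | 0.009 / 0.004 |
| Same HbA1c rule in all arms | 24% / 23% | 19% / 18% | −0.383 / −0.355 | −0.410 / −0.388 | 0.017 / 0.045 |
| HbA1c-related in control only | 33% / 32% | 22% / 22% | −0.222 / −0.203 | −0.406 / −0.402 | 0.178 / 0.197 (effect understated) |
| HbA1c-related in SMBG only | 22% / 22% | 26% / 25% | −0.535 / −0.549 | −0.390 / −0.389 | 0.135 / 0.149 (effect overstated) |

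Two other sets of assumptions, each with a true difference of 0.30 and SD 1.2%:

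- Exit depending on HbA1c above 8.5%, at rates that differ by arm (1,500 runs each). The 12-month model gave 0.228 (20% / 10%), 0.192 (25% / 10%) and 0.393 (10% / 25%), errors of 0.072, 0.108 and 0.093. The longitudinal estimates were 0.297, 0.297 and 0.299.
- Correlation 0.7, mean 9%, exit possible only above 8.5%. With the same rule in all arms, bias was about 0.01 or less. With rates differing by arm and exit following the last observed value, one run gave 0.251 against 0.298 for the longitudinal model (bias 0.049); a repeat put the bias near 0.04. With exit following the current, unrecorded value (drop-out 30% control, 11% SMBG), the estimates were 0.215 and 0.250. The bias falls from 0.085 to 0.050, so (0.085 − 0.050) / 0.085 = 41% is removed. A repeat put the bias at 0.07–0.08, with 30–50% removed.

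**5. Precision.** In the set with exit above 8.5% and 1,500 runs, the empirical SE fell from 0.129 to 0.123, 0.141 to 0.130 and 0.130 to 0.122, that is by 4.7%, 7.8% and 6.2%. In the main simulation the fall was smaller, from none to about 4% (0.124 to 0.119 at most).

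**The case against.** The strongest reply is that the plan does not contradict itself. The statement about withdrawals concerns the analysis as a whole and is qualified by possibility. Someone who leaves after month 6 does appear in the 3- and 6-month secondary analyses, up to the time of leaving. Baseline-adjusted analysis at a fixed time point is a standard primary method, imputation before the linear model is not excluded, and a condensed article may leave missing-data handling to the full protocol or the SAP. Much of this stands. A reader might infer that the interim values are ignored altogether or that the plan breaks its own promise. The text supports neither: the values are left out of the primary model only, and the promise is qualified. What remains is that the article does name a primary model, and as named it leaves out measured HbA1c for exactly the participants the statement is about.

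A reader might also infer that leaving is known to depend on study HbA1c. Study results are withheld from the participant, the nurse and the care team. The SMBG arms are managed at study visits on meter readings and the control arm by usual care. The one exception is the flag to the GP for a deteriorating control participant, and that is not a withdrawal rule. Exit is probably related to glycaemia, but partly through readings outside the recorded HbA1c series. This weakens the claim of bias from recorded HbA1c and also limits how much a longitudinal model can cure.

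Finally, the larger bias figures need exit patterns that differ by arm, which the protocol nowhere states. The open design, the different routes of glycaemic management and the control-only flag make a difference plausible, not established. The 33% allowance should not be used to enlarge the loss, since the protocol says drop-out was likely to be smaller.

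**Conclusion.** The point holds in a limited form. As stated, the primary model leaves out participants without a 12-month value, about 90–112 of 450 at the back-calculated 20–25% drop-out, and their interim HbA1c serves only secondary analyses. Under the assumed exit models the resulting bias is about 0–0.05 percentage points if the exit pattern is the same in all arms. It is about 0.04–0.20 in either direction if the pattern differs by arm; the upper end is half of the 0.40 effect implied by the revised effect size. These sizes rest on assumed correlations, means and exit rules and are not predictions for this trial.

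It would go too far to say that the primary result will be biased, or that a repeated-measures model would make it unbiased. The longitudinal model removes nearly all the bias when exit follows recorded HbA1c, and about 30–50% when it follows unrecorded current glycaemia. The precision gain is modest, about 5–8% in one set of simulations and 0–4% in another. The case for change is that the stated method can be improved cheaply with data already scheduled.

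**What to change.** Make the primary analysis a repeated-measures mixed model of HbA1c at 3, 6, 9 and 12 months, with arm by visit, baseline HbA1c by visit and an unstructured covariance. Include every randomised participant with at least one post-baseline value, and keep the 12-month group contrasts as the primary estimates. An acceptable alternative is to impute the missing 12-month values from baseline and interim HbA1c by arm and then fit the stated linear model.

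Keep the 12-month model in completers as a sensitivity analysis. Because missing at random given recorded HbA1c is only approximate here, add a delta-adjusted analysis that shifts the values imputed after withdrawal, with shifts allowed to differ by arm. Report withdrawals and insulin starts by arm, with the last observed HbA1c, so that readers can judge which exit pattern applies. Reword the sentence on withdrawn participants to say which analyses use their data.

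The cost is plan wording and slightly more programming; no new data are needed and the sample size does not change. Participants who leave before month 3 would still add no post-baseline value.

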### Setting and site selection

The study is being conducted at primary and secondary care sites across Wales and England. Larger primary care (GP) practices in Wales, defined as those with a practice population greater than 9000, with over 500 people on their Diabetes Disease Register of whom 20% or more had sub-optimal blood glucose control according to Quality and Outcomes Framework (QoF) data, were initially approached to take part in the study as recruiting sites. Smaller, research active practices were also invited to participate. Diabetologists working in secondary care across Wales were invited to be involved by working in partnership with GP practices i.e. Patient Identification Centres. In addition, two sites in England, one in primary care and the other in secondary care, expressed an interest in taking part and were accepted, making a total of 16 centres (nine primary care sites and seven secondary care sites).

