### Randomisation

Following acceptance into the study, participants will be randomised into one of three treatment groups. The randomisation procedure uses study site and previous experience with SMBG (Yes/No) as stratifying factors, and aims to allocate approximately equal numbers of participants in the three groups overall, by site and by previous experience. Randomisation will be performed remotely by the Swansea Trials Unit (formerly West Wales Organisation for Rigorous Trials in Health and social care (WWORTH)). Randomisation will be via email using a central database.

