### Sample size

Initial sample size considerations were based on previous data in which the response within each subject group was normally distributed with standard deviation of 13 mmol/mol HbA1c (1.2%). If the true difference in the experimental and control means is 0.3%, (3 mmol/mol) (corresponding to an effect size of 0.25), we will need to study 378 experimental subjects and 189 control subjects to be able to reject the null hypothesis that the population means of the experimental and control groups are equal with probability (power) 0.8. The Type I error probability associated with this test of this null hypothesis is 0.05. In summary, allowing for up to approximately 33% drop-out (to include participants who convert to insulin), a total of 850 participants are required (*n* = 284 per treatment group).

Following the recruitment of the first participants, although no formal interim analysis was proposed or undertaken, initial routine checks on data quality following recruitment of the first wave of participants provided an opportunity to review some of the assumptions underpinning our original sample size calculations. It became obvious that if we remained with our initial inclusion criteria of HbA1c (≥64 mmol/mol/ ≥8% to ≤97 mmol/mol/ ≤11%) a large number of participants would be missed. We therefore modified the criteria to ≥58 mmol/mol (7.5%) to ≤119 mmol/mol (13%). The review also showed that, first, the drop-out rate was likely to be smaller than originally expected and, second, that our original estimate of an effect size of 0.25 seemed to be conservative, with evidence to support increasing this to 0.333.

With all other elements in sample size considerations held fixed, the combined effect of these changes means that a total sample size of between *n* = 398 and *n* = 424 would be sufficient to achieve the study aims. Our revised target is now 450 (*n* = 150 per treatment group), which is higher and enables us to be confident that the proposed sample size will prove to have sufficient statistical power for our planned analyses and reports.

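### The stated primary model omits the two stratification factors (site and previous SMBG experience); if they predict 12-month HbA1c beyond baseline, the test is slightly conservative and a little power is forgone

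*Protocol article*

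**What the plan says.** In the Randomisation section, the allocation procedure "uses study site and previous experience with SMBG (Yes/No) as stratifying factors". The stated intention is a near-even split across the three arms, both in total and within the levels of each factor. Under Setting and site selection there are 16 centres, nine in primary care and seven in secondary care.

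In the Statistical analysis plan section, 12-month HbA1c is to be analysed with a "general linear model with baseline values and a nested set of group identifiers included as explanatory covariates and factors". The sentence that follows tests efficacy on the parameters for these group identifiers, so they are the treatment groups and not the sites. Secondary measures are to be "analysed using the approach outlined above for the primary measure", with linear models for continuous outcomes and logistic models for binary ones. No other section brings either stratification factor into an analysis.

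**The concern.** Balancing the groups within prognostic strata takes between-stratum variation out of the treatment contrast. A model without the strata leaves that variation in its residual, so it reports a standard error larger than the true sampling SD of the estimate. Confidence intervals are then too wide, the test rejects less often than 5% under the null, and part of what stratification bought is not collected.

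Both factors could plausibly matter. The centres mix primary and secondary care, control participants are managed by their usual provider, and previous SMBG use bears directly on the intervention. The same model form is passed on to the secondary outcomes.

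**Working it through.** **Inputs from the article.** Two-sided 5% level (Statistical analysis plan). From Sample size: power 0.8; SD 1.2% HbA1c; difference 0.3% (effect size 0.25); 378 experimental and 189 control participants; revised effect size 0.333; revised need 398 to 424; target 450.

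**Input not in the article.** R², the share of residual variance after baseline HbA1c that the strata explain. It is assumed to lie between 0 and 0.10, with 0.20 as an outer case.

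**1. Reproduce the plan's figures.** With 2:1 allocation, n(control) = (1.960 + 0.842)² × (SD/difference)² × (1 + 1/2).
- Effect size 0.25: 7.849 / 0.0625 × 1.5 = 188.4, so 189 control and 378 experimental, 567 in all. This matches exactly. 567/(1 − 0.33) gives 847 and 567/(1 − 1/3) gives 851, against the stated 850.
- Effect size 0.333: 7.849 / 0.1109 × 1.5 = 106.2, so 107 + 214 = 321 analysed. The stated 398 to 424 then implies drop-out of 1 − 321/398 = 19% to 1 − 321/424 = 24%.

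**2. Effect of omitting the strata.** Set the residual SD to 1, taking no credit for baseline HbA1c, as the sample size calculation does. With 107 control and 214 experimental participants, the standard error reported without the strata is √(1/107 + 1/214) = 0.1184. Under balanced stratified allocation the true sampling SD is 0.1184 × √(1 − R²). Hence:
- Overstatement of the standard error: 1/√(1 − R²)
- Type I error: 2 × [1 − Φ(1.96/√(1 − R²))]
- Power, strata omitted: Φ[(0.333/0.1184 − 1.96)/√(1 − R²)]
- Power, strata included: Φ[0.333/(0.1184 × √(1 − R²)) − 1.96]

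At R² = 0.10, √0.90 = 0.9487. The standard error is 1/0.9487 = 1.054 times the true value. Type I error is 2 × [1 − Φ(2.066)] = 3.9%. Power is Φ(0.8525/0.9487) = Φ(0.899) = 81.6% without the strata and Φ(2.965 − 1.96) = Φ(1.005) = 84.2% with them.

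| R² | SE too large by | Type I error | Power, omitted | Power, included | Points lost |
|---|---|---|---|---|---|
| 0 | 0% | 5.0% | 80.3% | 80.3% | 0 |
| 0.02 | 1.0% | 4.8% | 80.5% | 81.1% | 0.5 |
| 0.05 | 2.6% | 4.4% | 80.9% | 82.3% | 1.4 |
| 0.10 | 5.4% | 3.9% | 81.6% | 84.2% | 2.7 |
| 0.20 (outer case) | 11.8% | 2.8% | 83.0% | 88.2% | 5.2 |

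Differences were taken before rounding. With all 150 per group analysed, the loss at R² = 0.10 is 1.4 points (92.6% against 93.9%).

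**3. Simulation check.** 16 sites by two experience strata, blocks of three within strata, 107 per group, 2,000 runs per setting. At R² = 0.10, type I error was 4.2% without the strata and 4.9% with them, and power was 80.7% against 83.2%. At R² = 0.20 the figures were 3.0% against 5.4%, and 82.2% against 89.0%. At R² = 0 the two models were practically the same. The results agree with the formulas within simulation error. The blocks are an assumption, since the article states only the aim of near-equal numbers and not the allocation method.

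**The case against.** The best answer is that this is a condensed article, the full statistical analysis plan is not shown, and a complete covariate list is usually left to it. The sentence does not say that its terms are the only ones, and previous SMBG experience is known at baseline, so it might be meant by baseline values. Part of this stands: the full plan may already contain both factors. But the article is not silent on covariates. It names the model's terms, and the list does not match the design. The plain reading of baseline values, straight after 12-month HbA1c, is the baseline value of the outcome, and that reading could not cover site in any case.

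It is also right that the effect is conditional. If the strata explain nothing beyond baseline HbA1c, the two models perform alike, and nothing in the article fixes R².

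Four stronger inferences are tempting and are not supported.
- **That the trial becomes underpowered.** The sample size calculation takes no credit for the strata. For its pooled contrast, power without them is 80.3% to 81.6% over the assumed range at 321 analysed, still above the planned 80%, and the target of 450 exceeds the stated need of 398 to 424.
- **That type I error is inflated.** It moves the other way.
- **That a site term would deal with differences in delivery between sites.** The article does not say that one team delivers the intervention at each site. Delivery differences would arise in the SMBG groups only, which is treatment-by-site heterogeneity and is not addressed by a site main effect.
- **That the standard-error argument carries straight over to the logistic models.** There, adding prognostic factors also changes the odds ratio being estimated, from marginal to conditional.

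**Conclusion.** The point holds in a limited form. The stated model departs from the design by leaving out both stratification factors. If they explain 0 to 10% of the residual variance, the standard error is 0 to 5% too large, type I error runs from 5.0% down to 3.9%, and 0 to 3 points of power are lost relative to the adjusted model. The analysis as stated remains valid but conservative.

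These figures rest on the assumed R², near-complete balance within strata, 321 participants analysed, and the pooled SMBG-versus-control contrast at effect size 0.333 and an undivided two-sided 5% level. They do not cover the comparison of the two SMBG groups, or the multiplicity allowance that the article mentions without specifying. The change is worth making because it is nearly free, not because the trial depends on it.

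**What to change.** In the Statistical analysis plan section, add study site and previous SMBG experience (Yes/No) to the primary linear model and to the linear models for the secondary outcomes. Site can be a fixed effect. If some sites are small, use a random intercept or a pooling rule, chosen before outcome data are examined by group.

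If the factors also go into the logistic models, state that the odds ratio is then conditional on them, and use a random intercept for site where outcomes are sparse.

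The cost is a few sentences and, with site fixed, 15 + 1 = 16 degrees of freedom out of more than 300. Both factors are already recorded at randomisation, and the sample size does not change. If the full statistical analysis plan already includes them, only the published description needs to be brought into line.
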